The research is also limited by the fact that the available scientific literature on empathy interventions in healthcare professions students is primarily from high-income countries in North America and Europe (35). Relevant research from Asia is notably scarce, with a recent review (20) identifying only one such study, conducted in China (37). A later review focusing on qualitative aspects of empathy education interventions (38) identified another study, also from China (39). We are aware of only one relevant intervention study conducted in Singapore; this work involved an evaluation of a short empathy-training course for pharmacy students (40).

Lastly, intervention studies are typically conducted in students from a single healthcare discipline (20, 22, 36, 38). For instance, Winter’s review (2020) identified only one study that included healthcare students from multiple disciplines (41). Relatedly, most studies focused on medical and nursing students, with less research on pharmacy students and very little on dental students (42).

We responded to the call for mixed-methods longitudinal intervention research on empathy in healthcare professions students (3, 6, 35) and conceived a study recruiting freshmen dentistry, medicine, nursing and pharmacy students at the National University of Singapore. The primary aim of our study is to examine the effects of consecutive courses of a novel Common Core Curriculum for healthcare professions students that emphasize understanding patients, communication, and other critical areas of professionalism on empathy. Our secondary aims are: (a) Examining the effects of the novel curriculum on intentions to provide empathic care, (b) Studying the association between engagement in courses of the novel Common Core Curriculum and empathy as well as intentions to provide empathy care, (c) Exploring perspectives on and experiences with courses of the new Common Curriculum in relation to empathy and patientcare, and (d) Examining trajectories of empathy and intentions to provide empathy care beyond the novel Common Core Curriculum.

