#### Engagement in teaching and learning activities

Following each of the three courses, we administer an instrument to assess students learning engagement in various domains. The importance of engagement beyond the cognitive domain to achieve significant learning has been described (67, 68). For example, connecting with fellow learners can raise confidence and contribute to more positive attitudes toward a course. This, in turn, can raise the emotional desire to learn, resulting in more time and effort being invested in engaging with learning materials, ultimately impacting learning outcomes (69–71). Some suggestive evidence for the link between engagement and empathy has been reported in the context of medical students’ learning communities (72). Researchers observed that valuing aspects of social, collaborative and behavioral engagement was associated with empathy. As such, engagement in one or more domains may impact the development of empathy.

We drew 12 items from the Online Student Engagement Scale (OSE) and made minor modifications for our purpose (73). The instrument will enquire about the following domains of learner engagement: behavioral and cognitive engagement (learning efforts-5 items), emotional engagement (interest and commitment-4 items), social and collaborative engagement (contributing and connecting-3 items). Students will assess how well certain behaviors, thoughts and feelings describe them in relation to each course on a 5-point Likert scale ranging from ‘describes me perfectly’ to ‘does not describe me at all’. An example item reads ‘Participating actively in group-project discussions.’ Validity and internal consistency (alpha = 0.91) of the OSE are satisfactory as assessed in university students in the United States.

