### Sample size and data analysis—survey questionnaires

#### Sample size calculation

We conducted sample size calculations to estimate the number of participants required for an adequately powered analysis of the effect of the three courses under investigation on empathy as measured with the JSE-HPS. Considering a small effect size of 0.2 (20), a power of 80% and a two-tailed significance level of 0.05 we would need 199 participants at Follow-up 3. To account for an expected significant drop-out of >50% over time we aim to recruit 400 students into the study.

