#### Data analysis

To estimate the overall effect of the three courses on empathy and empathic care intentions across all students, we plan to conduct within-group t-tests. Repeated measures ANOVAs are planned to investigate the interactions between time and socio-demographic variables as well as engagement in teaching and learning activities on empathy and empathic care intentions. Significant interaction effects will be followed up with post-hoc tests and simple effects analysis as appropriate. Significant main effects will be followed up with post-hoc tests. The significance level will be set at 0.05. Data will also be plotted to visualize the results.

Free-text comments will be analyzed using qualitative thematic analysis (74). We will employ an inductive approach allowing the data to guide the generation of categories, themes and subthemes. We will first familiarize ourselves with the data by reading responses multiple times. Following this, we will conduct open coding of responses to capture all relevant content. We will then organize the codes into categories based on the overall topic they reflect. Within categories, we will identify themes and subthemes before crafting a narrative that will be supported by excerpts from the responses.

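### For aim (b) the only named method is repeated measures ANOVA with group-type follow-up, although engagement and age are recorded as numbers; they should be analysed as continuous terms

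*Protocol article*

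**What the plan says.** Aim (b) in the Introduction of the protocol article is "Studying the association between engagement in courses of the novel Common Core Curriculum and empathy as well as intentions to provide empathy care".

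Under Engagement in teaching and learning activities, the instrument is described thus: "We drew 12 items from the Online Student Engagement Scale (OSE) and made minor modifications for our purpose". The items fall into three domains of 5, 4 and 3 items. Each is answered on a five-point scale, and the instrument is given after each of the three courses. Under Demographic information, age is collected in years; course of study, gender, ethnicity and housing type are categories.

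Under Data analysis (survey questionnaires), the overall effect is estimated "across all students, we plan to conduct within-group t-tests". For the other variables, "Repeated measures ANOVAs are planned to investigate the interactions between time and socio-demographic variables as well as engagement in teaching and learning activities". The follow-up rule is: "Significant interaction effects will be followed up with post-hoc tests and simple effects analysis as appropriate". The next sentence sends significant main effects to post-hoc tests, this time without the closing qualifier. The section names no covariate, regression or slope.

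Under Sample size calculation, with a standardised effect of 0.2, 80% power and "a two-tailed significance level of 0.05 we would need 199 participants at Follow-up 3", the recruitment target is 400.

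**The concern.** Aim (b) is a question of degree: does more engagement go with more empathy? The natural answer is a slope. Post-hoc tests compare the levels of a factor, and a numeric score has no levels until someone cuts it. Read plainly, the named method and its follow-up therefore point towards grouping engagement, and also age if age is among the socio-demographic variables meant.

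Grouping would have three costs. Power falls. The answer becomes a contrast between groups, with no estimate per unit of engagement. And the result depends on where the cut is placed; the article fixes no cut, so one could be chosen after the data are seen. The three engagement measurements also relate to different courses, which a conventional repeated measures ANOVA with one fixed value per student does not handle easily.

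**Working it through.** **1. The plan's own figure.** Inputs from Sample size calculation: d = 0.2, two-sided alpha 0.05, power 80%. The normal approximation for a paired comparison is ((1.960 + 0.842)/0.2)² = 196.2, so 197. The exact paired t-test (noncentral t) gives 199, with power 80.2%. For 50% loss, 199/(1 − 0.5) = 398, in line with 400. The figure reproduces. It serves the within-group t-test, not aim (b).

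**2. Information kept after grouping.** The documents give no number of groups, so 2 to 5 equal-sized groups are assumed, with a normal score. With cut-points c_0, …, c_k and normal density φ, the mean of group i is m_i = k[φ(c_{i−1}) − φ(c_i)]. The share of information kept is e_k = (1/k) Σ m_i².

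- Two groups: m = ±2φ(0) = ±0.798, so e = 0.798² = 2/π = 0.637.
- Three groups: cuts at ±0.431, m = −1.091, 0, +1.091, so e = (2/3) × 1.091² = 0.793.
- Four and five groups, in the same way: 0.861 and 0.897.

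**3. Power at n = 199.** This n is borrowed from the primary calculation as an illustration. The correlation with 80% power when the score is numeric is ρ = 0.196 (ρ² = 0.0383). For k unordered groups, ρ_k² = e_k ρ². The omnibus F-test has k − 1 and 199 − k degrees of freedom and noncentrality 199 × ρ_k²/(1 − ρ_k²).

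| Form of the score | Information kept | Loss | Effective n (199 × e) | Noncentrality | Power |
|---|---|---|---|---|---|
| Numeric | 100% | 0% | 199 | 7.93 | 80% |
| 2 groups | 63.7% | 36% | 127 | 4.97 | 60% |
| 3 groups | 79.3% | 21% | 158 | 6.24 | 59% |
| 4 groups | 86.1% | 14% | 171 | 6.78 | 57% |
| 5 groups | 89.7% | 10% | 178 | 7.08 | 53% |

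More groups keep more information, but the extra degrees of freedom of an unordered test use up the gain.

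**4. Cross-check by Fisher z for a median split.** √(199 − 3) = 14. For r = 0.20: 14 × atanh(0.20) = 2.84, power 81%. After the split, r = 0.20 × 0.798 = 0.160, 14 × atanh(0.160) = 2.25, power 62%. For r = 0.15 the same steps give 56% and 39%.

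**5. Sensitivity to shape.** A median split loses 25% for a uniform score, 35% for a moderately skewed one (beta 5, 2) and 47% for a strongly skewed one (gamma, shape 1.5).

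**The case against.** The strongest reply is that the article never says that engagement or age will be grouped. It gives no cut and no high and low categories. A repeated measures general linear model accepts a numeric covariate and its interaction with time, and simple effects can be probed at chosen covariate values. The follow-up rule for interactions carries a qualifier. Post-hoc tests have an obvious use for time and for the categorical variables, so the generic follow-up sentences need not be aimed at engagement. Age is not named in the Data analysis section, no single engagement total is defined, and predictor coding may stand in a full analysis plan that is not shown. If ordered groups were used with a one-degree-of-freedom trend test, 79%, 86% and 89% of the information would be kept with three, four and five groups, without the degrees-of-freedom penalty.

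Most of this stands. A reader might infer that the plan forces numeric scores into groups and so discards about a third of the information. The text does not support that: grouping is an inference, and a third fits only a median split of a roughly normal score.

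A reader might also infer that engagement will be analysed without programme, so that differences between programmes pass for an effect of engagement. That is not supported either. The article does not say that the ANOVAs are run one factor at a time. Any false-positive rate put on this would rest on assumed variance shares and on perfect alignment of the programme means.

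What the reply does not remove is that the article does fix a method and a follow-up procedure for aim (b). Both fit groups better than scores, and the main-effects sentence carries no qualifier.

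**Conclusion.** The point holds as a mismatch between the named method and the variables it is to serve, with a loss that is conditional on grouping. If the scores stay numeric, nothing is lost. If they are grouped, the loss for a roughly normal score runs from 10% (five groups) to 36% (median split). Power at n = 199 then falls from 80% to about 53-60% under unordered testing. These figures assume equal-sized groups, a linear relation and 199 students in the analysis. Engagement is measured after each course, so earlier analyses may have more students.

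The primary within-group comparison and its sample size are untouched. This is a cheap improvement for a secondary aim and does not threaten the main result.

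**What to change.** In the Data analysis section, replace the repeated measures ANOVA for engagement (and for age, if it is used) with a linear or mixed model in which they are continuous terms. The outcomes are follow-up empathy and follow-up care intentions. The baseline score of the same outcome and the programme go into the same model. A mixed model can also take engagement course by course. Report the slope with its 95% CI, check linearity with a plot or spline, and use groups for display only. ANOVA-type comparisons with post-hoc tests can stay for the categorical variables.

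The cost is a change of wording; every variable is already collected. The one downside is the linearity assumption, which the plot or spline checks.

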### Data collection—interviews

Interview procedures and reporting were guided by the Consolidated Criteria for Reporting Qualitative Research (COREQ) checklist (75).

Experienced qualitative researchers working in the healthcare or education sector will conduct semi-structured interviews following the completion of Course 3, marking the end of the Common Core Curriculum. Utilizing a pre-piloted interview guide, open-ended questions and prompts will be used to explore three broad areas with research participants: reasons for selecting their healthcare profession and experiences with the study program, perceptions and skills pertaining to patient care and empathy, and the contributions of the Common Curriculum courses on perceptions and skills related to patient care and empathy. Throughout the data collection period, the interview guide will be iteratively refined to explore emerging themes and topics previously not considered.

Interviews will be conducted in English via widely used videoconferencing platforms such as MS Teams or Zoom. Interviews will be audio-recorded using platforms built-in features. Field notes of interviews will supplement the audio recordings.

#### Sampling

We will employ a purposive sampling strategy to ensure diversity in experiences and perspectives are captured. We aim to recruit dentistry, medicine, nursing and pharmacy students until saturation is achieved within each student group. We project that 30 students in total will be sufficient. However, we are mindful that more participants may be needed to draw a rich picture.

#### Data analysis

Verbatim transcripts of interviews will be used for a primarily inductive thematic analysis (74). Briefly, following line-by-line coding of transcripts, we will develop and iteratively refine broad analytical categories, within which we will identify themes and subthemes. Representative quotes from participants will be selected to illustrate the findings. Depending on the data, we will highlight differences of themes and subthemes across students from different programs.

## Conclusion

Empathy as a cognitive-behavioral attribute is important across healthcare disciplines and should be developed throughout tertiary healthcare training. Pedagogical strategies to do this are widely available and most scientific studies point to desirable effects when such strategies are being examined, often in isolation (35). Researchers also suggest that empathy-related education is acceptable to healthcare professions students with many reporting related instruction to be valuable. Unfortunately, many curricula lack a distinct focus on developing the essential socio-cognitive competency of empathy, leaving much to be desired (35). This observation prompted a growing number of educators and education researchers to call for a meaningful integration of empathy training into the curriculum so as to nurture healthcare professionals who have the skills to cure, but also the attitudes and competencies to care (76–78).

With the mixed-methods longitudinal intervention study described in this manuscript, we will examine the effects of three consecutive courses of a novel Common Core Curriculum for Healthcare Professions Students on empathy in freshmen dentistry, medicine, nursing and pharmacy students enrolled at the National University of Singapore. Findings will provide insights into the potential of integrating empathy-related education into the curriculum for healthcare professions students and inform us about iterative changes we might need to make to enhance an anticipated impact.
